**Protocol Number:** 818540

**Principal Investigator:** [name]

**Protocol Title:** Implementation of Prolonged Exposure in the Army: Is consultation necessary for effective dissemination?

**Short Title:** The Post-Traumatic Stress (PTS) Study

**Protocol Description:** This study will examine whether Prolonged Exposure (PE) for posttraumatic stress disorder (PTSD) can be successfully disseminated and implemented in the Army. 120 mental health providers will attend a 4-day PE workshop and will receive in-depth case consultation or no additional consultation following the workshop. Providers will complete surveys about their therapy practices. Patients seeking care for PTSD from providers will be recruited and consented to assess treatment response.

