**2.4. Method for Assigning Subjects to Groups**

The study proposes to enroll approximately 100 participants in each condition. Participants will be randomized to conditions by a computer-based random list generator.

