**6. Study Design**

**Phase***

Not applicable

*6.1. Design*

This is a randomized clinical trial comparing two methods of training mental health providers in Prolonged Exposure (PE) treatment for Posttraumatic Stress Disorder (PTSD). Two hundred (200) mental health providers at three medium-to-large CONUS Army installations will be randomly assigned to either Standard PE training or Extended PE training. All providers will receive a 4-day PE workshop, along with the distribution of training materials and treatment manuals, conducted at the military site by the Overall Study PI, [name], and her team. Following the 4-day workshop, participants randomized to the Extended PE training will receive weekly phone consultation with a PE expert on two PE therapy clinical cases followed by twice monthly telephone consultation as needed for six months. Participants randomized to the Standard PE training group will not receive any additional consultation following the workshop. Providers will not be required to use PE therapy to treat their patients with PTSD; using PE will be optional. A major outcome of this study is the proportion of the providers PTSD patients that are offered PE. The mental health outcomes of providers PTSD patients will also be monitored as a second major outcome. Patients seeking care for PTSD from participating providers will be recruited, consented and offered treatment for PTSD and related problems to prospectively and systematically assess what type of treatment they are offered and their response to treatment.

*6.2. Study duration*

The study is expected to start in May 2014 and end in May 2017. Subject recruitment and data collection will mostly occur in years 2, 3, and 4. Data analysis will occur in year 4.

*6.3. Resources necessary for human research protection*

Describe research staff and justify that the staff are adequate in number and qualifications to conduct the research. Describe how you will ensure that all staff assisting with the research are adequately informed about the protocol and their research related duties. Describe access to a population that would allow recruitment of the targeted number of subjects. If medical or psychological services as a consequence of the research, describe how the subject will be referred to those services. Describe your facilities and justify that the facilities are adequate. Verify that there is sufficient time to conduct and complete the research.

*6.4. Research Staff*

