The second set of Objectives concerns changes in therapist attitudes. The analysis model will be mixed effects regression as above, with intervention arm the primary independent variable and repeated measures at post-consultation and at two and three years. The dependent measures will be summary scores derived from the Implementation Surveys, using sums of relevant items as appropriate to operationalize therapist self-efficacy, satisfaction and expectations for change. We anticipate that changes in therapist attitudes may appear very quickly in the training process, influenced by expectations about consultation and supervision at the earliest stages and experience of training as it is received.

The third set of Objectives concern changes in patient outcomes, specifically PTSD symptom severity, other symptoms, dropout, and satisfaction with treatment. The analysis design for continuous measures based on self-report scales is simple analysis of (co)variance on post-treatment outcomes (or equivalently, change), comparing intervention arms using pre-treatment measures as covariates. If dropout data are available at the individual patient level, simple chi-square, logistic regression or generalized mixed effects models will be used to compare interventions. For all patient level outcomes, mixed models may be needed because patients are nested within therapists. Preliminary analyses will explore the need to include therapist as a random design effect to account for possible clustering effects (Crits-Christoph & Mintz, 1991). For the therapist level outcomes, the impact of baseline patient (or therapist) characteristics that are confounded with intervention condition will be evaluated using analysis of covariance.

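### Providers are randomised, but adjustment of patient outcomes for provider clustering depends on an undefined preliminary analysis; it should be fixed in advance.

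*Protocol*

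**What the plan says.** Section 6.1 (Design) makes the provider the unit of randomisation: "Two hundred (200) mental health providers at three medium-to-large CONUS Army installations will be randomly assigned to either Standard PE training or Extended PE training". Sections 7.2 and 7.7 recruit patients through those providers, so each patient belongs to one provider and takes that provider's arm.

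Section 8.2 (Analysis Plan) then covers the patient outcomes: "The third set of Objectives concern changes in patient outcomes, specifically PTSD symptom severity, other symptoms, dropout, and satisfaction with treatment". It makes four statements about their analysis:

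- Continuous outcomes: "The analysis design for continuous measures based on self-report scales is simple analysis of (co)variance on post-treatment outcomes", with pre-treatment measures as covariates and no therapist term.
- Dropout, if individual data are available: "simple chi-square, logistic regression or generalized mixed effects models will be used to compare interventions". No rule for choosing among the three is given.
- All patient-level outcomes: mixed models might be required because of the nesting.
- How that is decided: "Preliminary analyses will explore the need to include therapist as a random design effect to account for possible clustering effects".

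The section sets no threshold, test or other criterion for the last step. Nowhere does the protocol undertake to account for therapist regardless of what the preliminary analysis shows.

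**The concern.** Patients treated by the same provider tend to have correlated outcomes, and the training under test acts through the provider. A comparison that treats patients as independent then understates the standard error of the arm difference whenever the ICC is above zero. The dependence comes from the design, so it does not need to be shown empirically before it is allowed for. A preliminary look that finds no clear therapist effect does not show that there is none, especially with few patients per provider.

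A conditional rule with no criterion also leaves the model to be chosen after the data are seen. At stake are the p-values and intervals for the third hypothesis in section 5.2.1, that Extended training gives better patient outcomes.

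**Working it through.** **Inputs from the protocol.** The provider is the unit of randomisation (6.1). The number of providers is stated inconsistently: "120 mental health providers will attend a 4-day PE workshop" in the opening description, against "The study proposes to enroll approximately 100 participants in each condition" in 2.4, that is about 200 in all. That conflict is a separate matter, and both totals are used below.

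**Inputs assumed because the protocol gives none.** Two-sided alpha 0.05; patients per provider m = 3 to 5; ICC 0.05 to 0.15. There is no stated power, error rate or sample-size calculation to reproduce.

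**Step 1: error if therapist is left out.** With equal caseloads,

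DEFF = 1 + (m − 1) × ICC, and true error = 2 × [1 − Φ(1.96 / √DEFF)].

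Example: m = 5, ICC = 0.10 gives DEFF = 1 + 4 × 0.10 = 1.40, 1.96 / √1.40 = 1.656, and error = 0.098.

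**Step 2: chance that a pretest finds the clustering.** For a 5% F-test of therapist variance within arms, the ratio of expected mean squares is λ = DEFF / (1 − ICC). With K providers, power = P(F > F₀.₉₅ / λ) on K − 2 and K(m − 1) degrees of freedom. For m = 3, ICC = 0.05: λ = 1.10 / 0.95 = 1.158, and with K = 120 the power is 0.24.

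**Step 3: error of the test-then-decide rule.** This was simulated under no arm effect (20,000 runs per setting, equal caseloads, continuous outcome, no covariate). The simple test is used unless the 5% pretest is significant; otherwise the test uses therapist-level variance.

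Results with 120 providers:

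| m | ICC | DEFF | Error, therapist left out | Pretest power | Error, test-then-decide | Error, therapist always in |
|---|---|---|---|---|---|---|
| 3 | 0.05 | 1.10 | 0.062 | 0.24 | 0.055 | 0.050 |
| 3 | 0.10 | 1.20 | 0.074 | 0.57 | 0.055 | 0.050 |
| 3 | 0.15 | 1.30 | 0.086 | 0.85 | – | – |
| 5 | 0.05 | 1.20 | 0.074 | 0.50 | 0.059 | 0.052 |
| 5 | 0.10 | 1.40 | 0.098 | 0.92 | 0.055 | 0.052 |
| 5 | 0.15 | 1.60 | 0.121 | 0.996 | – | – |

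The two rows without simulated values are bracketed by ICC 0.10 (shown) and ICC 0.20, where test-then-decide gave 0.051 (m = 3) and 0.052 (m = 5).

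**Sensitivity.**
- *200 providers.* Error with therapist left out is essentially unchanged, because DEFF does not depend on the number of providers. Test-then-decide gives 0.052 to 0.053 for m = 3 or 5 and ICC 0.05 or 0.10.
- *Looser pretest (0.20 level), 120 providers.* Test-then-decide gives 0.050 to 0.054 in the same settings.
- *Uneven caseloads.* With an assumed coefficient of variation of 1 in caseload and 120 providers (6,000 runs), test-then-decide reached about 0.066. Leaving therapist out gave 0.077 (m = 3, ICC 0.05), 0.098 (m = 5, ICC 0.05) and 0.146 (m = 5, ICC 0.10). The protocol gives no basis for that coefficient.
- *Few patients per provider.* With m = 1, DEFF is 1 and there is no inflation. With m = 2, leaving therapist out gives 0.052 at ICC 0.02 and 0.056 at ICC 0.05.
- *Therapist always in.* Simulated error was 0.048 to 0.053 across all equal-caseload settings run.

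**The case against.** The strongest reply is that the protocol does not propose to ignore clustering. It names the nesting, applies that remark to all patient-level outcomes and undertakes to look. If the look is a formal test followed strictly, the error stays near nominal. The test misses mainly where little is at stake: it has power 0.24 at m = 3, ICC 0.05, where the simple analysis errs at 0.062, but power 0.996 at m = 5, ICC 0.15, where the simple analysis would err at 0.121. This stands, and it sets the size of the point. It does not remove the fault, because the protocol defines no such test. A rule that only explores the need can end anywhere between the adjusted analysis and the simple one.

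Four stronger readings are tempting and are not supported:

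- *That 6 to 12% is the error to expect.* It applies only if therapist is never modelled.
- *That chi-square is the default for dropout.* It is one of three listed options, and a generalised mixed model is another. The fault there is the open choice.
- *That CAPS-5 is assigned the simple analysis.* That sentence is limited to self-report scales, and section 2.2 describes CAPS-5 as a structured interview. The remark about mixed models does cover it, but only conditionally.
- *That the primary outcomes are affected.* Section 5.2.3 lists patient outcomes as secondary, although sections 5.1 and 6.1 call them a second major outcome. The provider outcomes of 5.2.2 are a separate set of objectives, for which 8.2 names mixed effects regression with repeated measures.

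It may also be said that a SAP, not shown here, could supply the criterion. It could, but the point does not rest on missing detail: the protocol itself states the simple analysis and the conditional rule.

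**Conclusion.** The point holds as a fault of conditional adjustment. The design creates the clustering and the protocol recognises it, yet whether it is allowed for is left to an undefined look at the data.

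Under the assumed alpha, caseloads and ICC, the likely cost is small (about 5 to 6% instead of 5%) if a formal 5% pretest is followed, and somewhat more with uneven caseloads. The worst case that the wording permits is about 6 to 12%. With one or two patients per provider, or an ICC near zero, it hardly matters. None of these inputs is in the protocol, so the true size cannot be settled from it.

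This should be fixed. It concerns formally secondary outcomes and calls for a change of wording; it does not invalidate the design.

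**What to change.** Replace the sentence on preliminary analyses in section 8.2 with a commitment along these lines:

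> Every patient-level comparison between arms, including CAPS-5 and dropout, will account for clustering by provider, whatever the estimated size of the provider effect. Models will include a random provider intercept, or will use provider-clustered robust inference (for example if the dropout model does not converge). The first-assessment value will be a covariate where one exists. The estimated ICC will be reported for each outcome.

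Change the sentence on continuous outcomes to match, name CAPS-5 explicitly, and remove the unadjusted chi-square and ordinary logistic regression options for dropout. A fixed term for installation and small-sample degrees of freedom are reasonable choices but are not needed to cure the fault.

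The cost is a few lines of text and slightly wider intervals. No new data are needed.

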**Deception**

*Does your project use deception?*

No

*Are you conducting research outside of the United States?*

No

**9. Confidentiality**

**Data confidentiality**

x Paper-based records will be kept in a secure location and only be accessible to personnel involved in the study.

x Computer-based files will only be made available to personnel involved in the study through the use of access privileges and passwords.

x Prior to access to any study-related information, personnel will be required to sign statements agreeing to protect the security and confidentiality of identifiable information.

x Wherever feasible, identifiers will be removed from study-related information.

*9.1. Subject Confidentiality*

Research files will be created for each study participant (provider and treatment-seeking patients). All data collection sheets will be coded. Research staff at each of the performance sites will assign a unique alphanumeric number to each participant and maintain the link between PHI and the code only at the local site. Research files will be maintained in a locked filing cabinet in a locked office that only study staff can access. From the data collection sheets, all coded research data will be entered into the study database that will be maintained by the University of Texas Health Science Center at San Antonio (UTHSCSA) using the same policies and procedures established for the South Texas Research Organizational Network Guiding Studies on Trauma and Resilience (STRONG STAR) PTSD Research Consortium. Access to the coded research data maintained by UTHSCSA will require a password-protected login available only to authorized Biostatistics and Data Management Core staff. Data will be stored in a password-protected centralized database server on a Windows 2003 platform using Microsoft SQL 2005. Security of the Database. The project uses two Dell Servers, both with RAID configured multiple hard drives as well as a separate external daily backup. The physical layer of the internal network infrastructure is a Gigabit Ethernet backbone maintained by UTHSCSA System and Network Operations (SNO).

- Firewalls: The University provides a series of CISCO firewalls and switched routers to provide the first line of campus security. Additionally, an external agency is responsible for monitoring firewall activity and event logs to provide an independent analysis of intrusion attempts and trends. STRONGSTAR employs an additional firewall appliance maintained by SNO at the entrance of its virtual network to further protect its resources.

- Network Design: The University has subdivided its network into Virtual Local Area Networks (VLANs). A VLAN-based network is used to subdivide users and servers based on both physical and operational parameters. A user must be physically mapped into a VLAN before any of its resources may be accessed. The University has designated a single VLAN for STRONGSTAR-specific resources.

- Public Zone: The public zone is a networking environment in which the University firewall will allow standard Internet traffic (and special secure shell access) to enter. The STRONGSTAR web servers (not database servers) reside in the campus public zone. The web server is configured to limit its internal access to a single computer (over a specialized and heavily monitored port) within the STRONGSTAR VLAN.

- Virtual Private Networking: The University offers a Virtual Private Networking (VPN) client application to access basic university resources; however, the STRONGSTAR firewall has an independent VPN capability (via the CISCO firewall). Users outside the STRONGSTAR VLAN may access computer resources through this encrypted VPN access. Access to the STRONG STAR website is restricted to SSL (128 bit) encrypted connections only. If FTP or application-driven email is implemented we will implement encryption for those services as required. Authentication is by username and password. The password is hashed (one-way-encrypted) using MD5 encoding so it is nearly impossible to reverse engineer the hash and get a person's password. Password length is restricted to a minimum length of eight characters to make brute force hacking difficult. After three failures the user is locked out for a period of one hour, making brute force hacking difficult. Access is logged making hacking attempts easier to discover. Users have access to only what they need to see and do by using the least-privilege access security scheme. To protect this data, STRONG STAR system has developed the concept of functional group access augmented with traditional application role-based access.

- A functional group can be any logical grouping of people or users (e.g., research sites, departments, working groups, etc.). Each authorized user is matched to one or more functional groups. As subjects are registered into the system, they are in turn mapped to the same list of functional groups. In addition, since a subject may belong to multiple functional groups (e.g., registered on multiple protocols), each time a group registers a subject, the protocol specific information is also mapped to the users functional group. To increase the granularity of the data access, an application may implement roles specific to the customers’ needs. A data manager may need to view (and edit) all of a subjects protocol-specified research data, a protocol coordinator may need to view specific data items, have no need to edit research data, but have the requirement to enter information specific to their associated research.

- The web server and database server are different machines. The database server is not accessible from the internet. The web service access to the database is using the least-privilege method of access. It only has read and write privileges to the database, no delete or alter. All free-form text fields are "cleaned" before being sent to the SQL engine for access to the database. This makes SQL Injection much more difficult. Also, because of the least-privilege access it would be nearly impossible for a hacker to do any damage to the data since the web server does not have any administrative privileges to the database. Monthly archives are made off all servers and saved for an extended period of time. Backups are spot-verified. Server operating system software is patched as updates are made available. Server logs are monitored for system problems and hacking attempts. All critical STRONG STAR data transactions are maintained in a series of audit and archive tables. Every member of the research team will be trained and monitored about how to handle and protect both medical and research records.

*Who will be responsible for ensuring research records are secured prior to destruction date?* Research staff named in the protocol and the University of Texas Health Science Center at San Antonio (UTHSCSA) STRONG STAR Data Core supporting this project.

*Destruction plan for research records: When and how will the research documents, data files, and the master code be destroyed?*

There is no plan to destroy research documents or data files. Participant identifiers and PHI for both mental health providers and patients seeking treatment will be destroyed upon closure of the study with the IRBs. Informed consent documents will be stored securely for three years following completion of the research; HIPAA authorizations will be stored for six years IAW Federal regulations. Video-recordings of training cases will be copied onto DVD at the individual performance sites, labeled with the providers study number, and mailed directly to the University of Pennsylvania Center for the Treatment of Anxiety for review as part of case consultation teleconferences using an express service (e.g., FedEx) and tracked for receipt. Following review with the participant provider, the tapes will be destroyed by the Center for the Treatment of Anxiety staff.

**Sensitive Research Information***

*Does this research involve collection of sensitive information about the subjects that should be excluded from the electronic medical record?*

No

*9.2. Subject Privacy*

Participants will be asked for consent for all study procedures. No procedures will be performed without prior consent of the participant. The link between study ID number and a participants' protected health information will be password protected, with limited access to study personnel. Only staff directly working on the study will interact with participants and their patients and have access to data. Participants will interact with study staff in private offices and on the telephone.

*9.3. Data Disclosure*

Data will not be disclosed to anyone who is not listed under Personnel. If information from this study is published or presented at scientific meetings, names and other personal information will not be used.

**Data Protection***

x Name Street address, city, county, precinct, zip code, and equivalent geocodes

x All elements of dates (except year) for dates directly related to an individual and all ages over 89

x Telephone and fax number

x Electronic mail addresses

Social security numbers

Medical record numbers

Health plan ID numbers

Account numbers

Certificate/license numbers

Vehicle identifiers and serial numbers, including license plate numbers

Device identifiers/serial numbers

Web addresses (URLs)

Internet IP addresses

Biometric identifiers, incl. finger and voice prints

Full face photographic images and any comparable images

Any other unique identifying number, characteristic, or code

None

**10. Consent**

*10.1. Consent Process*

